## Abstract

**Background:**

Abnormal health anxiety, also called hypochondriasis, has been successfully treated by cognitive behaviour therapy (CBT) in patients recruited from primary care, but only one pilot trial has been carried out among those attending secondary medical clinics where health anxiety is likely to be more common and have a greater impact on services. The CHAMP study extends this work to examine both the clinical and cost effectiveness of CBT in this population.

**Method/Design:**

The study is a randomized controlled trial with two parallel arms and equal randomization of 466 eligible patients (assuming a 20% drop-out) to an active treatment group of 5-10 sessions of cognitive behaviour therapy and to a control group. The aim at baseline, after completion of all assessments but before randomization, was to give a standard simple explanation of the nature of health anxiety for all participants. Subsequently the control group was to receive whatever care might usually be available in the clinics, which is normally a combination of clinical assessment, appropriate tests and reassurance. Those allocated to the active treatment group were planned to receive between 5 and 10 sessions of an adapted form of cognitive behaviour therapy based on the Salkovskis/Warwick model, in which a set of treatment strategies are chosen aimed at helping patients understand the factors that drive and maintain health anxiety. The therapy was planned to be given by graduate research workers, nurses or other health professionals trained for this intervention whom would also have their competence assessed independently during the course of treatment. The primary outcome is reduction in health anxiety symptoms after one year and the main secondary outcome is the cost of care after two years.

**Discussion:**

This represents the first trial of adapted cognitive behaviour therapy in health anxiety that is large enough to test not only the clinical benefits of treatment but also whether the cost of treatment is offset by savings from reduced use of other health services in comparison to the control group.

Cognitive behaviour therapy for Health Anxiety in Medical Patients (CHAMP)

**Trial registration:**

Current Controlled Trials ISRCTN14565822

## Background

Abnormal health anxiety - and its older synonym, hypochondriasis - is a relatively common problem in both primary and secondary medical care settings [1-3]. It also places a substantial burden on health services [4], as its central feature is sufficient fear of having a serious disease to lead to medical consultation, and, very commonly, this is followed by further investigations. This condition, despite its ubiquity and its ability to provoke considerable suffering, is often unrecognised or appreciated at a superficial level. Even when the condition is recognised, concerns over litigation may lead to expensive investigations being carried out unnecessarily. This may provoke further pathology when findings of marginal clinical significance are reported. The extra burden on services is particularly important in secondary medical care. Between 10 and 20% of all attenders at medical clinics have abnormal health anxiety [5-7] and patients often rotate between different clinics depending on the focus of their symptoms. The symptoms of abnormal health anxiety show little tendency to spontaneous resolution and persist for months in the absence of treatment [5].

The failure to detect this serious pathology is perhaps less surprising when there is a general belief that there is no adequate treatment. Pharmacological management is generally unsatisfactory but psychological treatment in the form of cognitive behaviour therapy (CBT) has been shown to be effective, mainly in primary care [8,9] and, more recently, in a secondary care medical clinic [10]. Although these trials suggest efficacy of this intervention, it is less clear if it has a significant impact on costs. Although the total costs were somewhat reduced in those receiving cognitive behaviour therapy in the only trial in secondary care, these only became manifest in the six months after treatment had been completed [10]. The CHAMP trial is the natural successor to these studies, and examines both efficacy and cost-effectiveness of this newly modified treatment over a two-year period.

## Research objectives

The main objectives of the CHAMP trial are to examine the clinical value, cost and cost-effectiveness of the administration of CBT in health anxious patients attending out-patient clinics in secondary care. Specifically we hypothesised that (i) between 5 and 10 sessions of health anxiety directed cognitive behaviour therapy using the Salkovskis/Warwick model [11,12] would be more effective than normal care in the clinic in reducing abnormal health anxiety recorded by changes in the Health Anxiety Inventory (HAI)[13] one year after randomisation to the trial, and (ii) the cost of the CBT and control are equivalent, the endpoint for this outcome is the cost of health service interventions at 2 years adjusted for baseline values.

The secondary hypotheses are that, compared with the control condition, health anxiety directed cognitive behaviour therapy will lead to significantly greater improvement in health anxiety at 3, 6 and 24 months measured using the Health Anxiety Inventory (HAI)[13], in self-rated generalized anxiety measured using the Anxiety section of the Hospital Anxiety and Depression Rating Scale (HADS-A)[14], in quality of life using the EQ-5D measure of health-related quality of life [15], and in social functioning using the Social Functioning Questionnaire (SFQ)[16], all at 6, 12 and 24 months, result in the loss of the diagnosis of hypochondriasis at 24 months using the criteria of the Structured Clinical Interview for DSM-IV [17] and will be a cost-effective use of resources, where improvements in outcomes (measured using the HAI and in QALYs) are considered worthwhile.

In addition we will test the hypotheses that health anxiety focused cognitive behaviour therapy will be less effective in patients who have additional comorbid pathology in the form of (i) obsessional symptomatology (using the Short Obsessive Compulsive Screening (SOCS)[18]), dependent personality (using the Dependent Personality Questionnaire [19]), and hypochondriacal and other personality disorders [20] (using the Personality Assessment Schedule-Quick Version (PAS-Q)[21]) and that these comorbid disorders will be associated with increased costs.

The study also allows prevalence estimates to be made for health anxiety in different age groups and in different medical clinics.

## Methods/Design

### Trial summary

The study proposed is a pragmatic randomized controlled trial with two parallel arms and approximately equal randomization of eligible patients to an active treatment group of 5-10 sessions of cognitive behaviour therapy or to a control group. During the course of baseline assessment an explanatory interview will be given about the nature of health anxiety; this will be the only specific intervention in the control group but there is some evidence that this is of benefit in its own right [10].

### Settings

Patients attending cardiology, endocrine, gastroenterology, neurology and respiratory medicine clinics in five general hospitals (Kings Mill, North Nottinghamshire; St Mary's Hospital, Paddington, London; Charing Cross Hospital, Fulham, London; Chelsea and Westminster Hospital, London; and The Hillingdon Hospital, Middlesex) were considered for the study. 107 consultants agreed to collaborate with the study and to allow their patients to be approached provided they were not considered inappropriate for the study on account of the severity of their physical pathology.

### Form of randomisation

After baseline assessment randomisation was carried out by a computerised system (Open Clinical Data Management System (Open-CDMS)) using block randomisation with no stratification in randomised blocks of four and six. The allocation was carried out by the UK Mental Health Research Network and was independent of CHAMP personnel.

### Target population and procedure

Patients attending clinics of the collaborating consultants, apart from those who have been specifically excluded (see below), were approached while waiting for their out-patient appointments and given the short form of the Health Anxiety Inventory (HAI)[13], a rating scale of 14 questions that takes 5-10 minutes to complete. Those that scored at least 20 on the scale were offered the opportunity to take part in the trial and given an information sheet about the study. Within a week of receiving the information sheet and agreeing to be contacted the researcher administered part of the Structured Clinical Interview for DSM-IV with questions covering the diagnosis of hypochondriasis, and if the patient satisfied the criteria for this diagnosis he or she was invited to give formal consent and complete baseline assessments. At this appointment all patients received a standard explanation of the nature and significance of health anxiety that put their problem into context, and this was followed by the assessments described below. After completion of the assessments the research assistant entered and registered each patient to an on-line system (OpenCDMS Clinical Data Management System) and this was automatically followed by the appropriate randomisation. The study coordinator was then informed of the details of the treatment arm allocation and passed on the details to the next available therapist. Equal allocation was made to either (i) active treatment group - between 5 and 10 60-minute sessions of cognitive behaviour therapy from a graduate researcher, or trained research nurse or equivalent professional, at the clinic backed up by three booklets specially written for patients, or (ii) a control group of normal care who would not receive specific treatment but had already received a short account of the essentials of health anxiety at baseline interview.

The patients were recruited over a 21 month period beginning in October 2008 and each will be followed up for two years. In addition to research assistants who were employed on the trial, help in recruitment was also provided by Clinical Studies Officers of the North London and East Midlands hubs of the Mental Health Research Network.

### Ethics

The study was approved by the Nottingham Research Ethics Committee 1 (08/H0403/56) to run on all the planned sites covered by the clinics.

### Inclusion and exclusion criteria

Patients suitable for inclusion were those who satisfied the criteria for excessive health anxiety above and were (i) aged between 16 and 75, (ii) permanently resident in the area, (iii) had sufficient understanding of English to read and complete the questionnaires, and (iv) had given written consent for the interviews, audio-taping of 50% of treatment sessions, and for access to their medical records. The presence of existing medical pathology, provided it was not new and requiring further investigation, was not a bar to treatment in the study. This decision was made as in an earlier study we found that many patients with existing pathology who also had high health anxiety benefited from the intervention [10].

Some of those who would otherwise satisfy the inclusion criteria above were excluded if (i) they were felt by their consultants to have a level of continuing major pathology that was too severe for them to take part in the study, (ii) they were currently being actively investigated for significant pathology suspected by the clinician and for whom cognitive behaviour therapy might confuse or cause distress, (iii) they had significant cognitive impairment, and (iv) they were currently under psychiatric care.

## Assessments

The following assessments were carried out at base-line only;

(i) personality assessment using the quick version of the Personality Assessment Schedule (PAS-Q)[21] but also including the questions from the hypochondriasis subsection of the full schedule [20],

(ii) the Short Obsessional Compulsive disorder Screener (SOCS)[18] (a set of 7 questions that identifies the likely presence of obsessive compulsive disorder, and

(iii) the Dependent Personality Questionnaire [18], an assessment of dependence traits. These are included as both dependent personality and obsessional symptoms associate with another condition may handicap or complicate treatment.

The remaining clinical assessments, in addition to the main health anxiety one (HAI) examined the presence of generalised anxiety and depression (measured with the HADS scale [14]) as these are common in patients with hypochondriasis, and also adversely affects quality of life (EQ-5D)[15], and social functioning (SFQ)[16]. These assessments were given at baseline and at 6m, 12m and 24m (or earlier and at intervening periods if drop-out or loss to follow-up was likely). To ensure the highest possible follow-up the intention was to contact patients after 18 months to be reminded of the 2 year assessment, and if for any reason (eg being out of the country), the final assessment might be made earlier. The HAI was also given at 3 months by post or by telephone with a research assistant. Service use data for the economic evaluation was collected using the Adult Service Use Schedule (AD-SUS), an interviewer-assessed instrument designed by one of the applicants and based on previous economic evaluations in adult mental health populations [22,23], and also by examination of computerised hospital records. AD-SUS data were recorded at baseline and at 6, 12 and 24 months. Where the AD-SUS data conflict with the data obtained from the computerised records the AD-SUS data will take precedence only when it refers to a contact at a hospital not included in the electronic data search, as the details of admission and investigations is more likely to be correct from official records than from personal retrospective recall. Data on workplace absenteeism and presenteeism [24] were also recorded at 6, 12 and 24 months follow-up. In addition the SCID-I hypochondriasis questions [17] are to be administered again at 24 months to determine if each patient still satisfies the requirements for DSM-IV hypochondriasis. All these instruments are given at face to face interview but also have the advantage that they can be given over the telephone if necessary, and this can be useful in reducing loss to follow up. All assessments are carried out by independent research assistants who have had no contact with the patient at other times and who are carefully masked to avoid disclosure of allocation (see below).

## Methods of overcoming bias

The independent central computerized system involved in randomization ensures no bias in allocation of treatments. As this is a single blind study there is always the danger of disclosure of the form of treatment by the patient, therapist or other investigators in the study. This is minimized by (a) patients being asked by research assessors not to disclose their treatment to the research assessors, (b) the assessors and therapists working in different areas, (c) ensuring that all follow-up interviews are conducted by a researcher is masked to the patient's allocation status. The procedure was that whenever a researcher was unblinded a different research colleague was asked to conduct all further follow-up interviews.

## Study interventions

### Cognitive behaviour therapy treatment arm

The aim is to replicate the conditions of treatment that would be likely to prevail in the future if the trial found benefit from CBT, as much as possible the planned cognitive behaviour therapy was given within or close to the clinic close to the clinic as patients are more likely to consider it to be an unexceptional aspect of their care, thus avoiding the potential for stigma associated with a referral to mental health services. At each centre we therefore trained a graduate research worker, research nurse or equivalent health professional to administer the treatment. Each patient was invited to receive between 5 and 10 sessions of cognitive behaviour therapy with additional adaptations for health anxiety developed by [name] and [name], which is reinforced by three booklets to be handed to patients at treatment sessions (Table 1). Each therapist received training from the senior practitioners in the study before taking on the care of patients.

**Table 1 T1:** Essentials of specific elements of cognitive behaviour therapy for health anxiety

Listing of all symptoms and how the patient interprets them
Formulation of worst fears

Introducing possibility of alternative explanations (eg pie charts and pyramids)

Evaluation of risk of disease

Considering the price paid for health anxiety

Exploring the hypothesis of fear of disease being more likely than actual disease

Building evidence by identifying symptom patterns that are related to those of anxiety (ie diary keeping)

Reducing behaviour that maintains health anxiety such as excessive bodily checking and reassurance seeking

Because of the need for training, recruitment was planned to be slower in the first three months of the trial compared with the later phases of the study. Following this initial period, therapists had fortnightly supervision until the last patients had been recruited and treated. Therapists were also given three booklets of cognitive behaviour therapy developed for health anxiety prepared for training during treatment.

## Training and Fidelity of Intervention

Four of the authors (PS, GS, DM and HT) were involved in the training of therapists. These four therapists, together with [name] (one of the originators of the treatment), are also involved in assessing treatment fidelity, by listening to a selection of taped sessions from each therapist.

Approximately half of all treatment sessions will be recorded and tapes or discs of these sessions given to patients to help in their progress. Fidelity will be tested using a health anxiety modification of the Cognitive Therapy Rating Scale [25] (the Health Anxiety Version; CTRS-HAV. The issue is important as better treatment fidelity with cognitive behaviour therapy has been associated with greater treatment effects [26,27].

## Sample size

We calculated sample sizes for both the primary outcome measure and the first secondary outcome measure, choosing the larger of the two for the study.

Based on the pilot study in a genitourinary medicine clinic [10], we assume that the true difference in the change of HAI between CBT and control at 1 year is 5.00 points and that the standard deviation for the change of HAI at 1 year is 7.58 points. With the above assumptions, the study will need 122 patients to detect the above difference with 95% power at a two sided 5% significance level. Taking into account an estimated drop-out rate of 20% drop-out, the sample size is therefore estimated to be 152 patients.

There remains no agreed approach to calculate the sample size required for an economic evaluation, particularly in areas such as health anxiety in which the willingness to pay for improvements in outcomes is unknown. Based on the pilot study, we considered that the CBT intervention would be cost-effective if it improved HAI score and was no more costly than the control treatment. The sample size calculation for the economic evaluation was therefore based on the total costs over 24 months being equivalent.

With a sample size of 186 per group, the study will have 80% power to reject the null hypothesis that the cost of the CBT and control are not equivalent (where the difference in mean costs is +/- £150) in favour of the alternative hypothesis that the means of the two groups are equivalent, assuming the expected difference in means is £0 and the common standard deviation is £580 (from pilot data).

The sample size is thus powered by the first secondary outcome of the CHAMP study, estimated as 466 patients, assuming a 20% drop-out by 24 months, leading to an estimated total of 372 completed with equal randomisation between groups. Thus with 466 patients, or fewer if the drop-out rate is less, the study is adequately powered to both detect the assumed difference in the primary outcome and assess the equivalence in the secondary economic outcome between CBT and control group. The analysis will close on the date on which the last patient has completed the two year follow-up.

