## Statistical analysis

All primary statistical analysis will use the intention-to-treat principle. The primary endpoint will be analysed using a mixed model with time, treatment, time × treatment interaction as fixed effects, baseline measurement as covariate, and patient as random effect. The treatment difference at 12 months together with its 95% confidence interval will be derived from the mixed model.

Missing data will be treated as missing at random in the above mixed model analysis and no imputation will be made. To assess the sensitivity of the result to this assumption, the last observation carried forward (LOCF) strategy will be used to compute the missing HAI at during the follow up visits. Other assessments will be analysed in a similar way.

The primary economic evaluation will only include those for whom complete data at baseline, 12 and 24 months follow-up are available. Sensitivity analysis will then include those cases with missing data, where LOCF will be used to account for missing data. The following baseline characteristics of study participants with available and unavailable service use data will be compared: centre, gender, living arrangements, ethnicity, marital status, education, EQ-5D.

For each piece of service use information collected with the AD-SUS, a unit cost will be applied and the total costs calculated. The total cost per participant is calculated by summing all costs. All unit costs will be for the financial year 2008-2009. Costs in the second year will be discounted at a rate of 3.5%, as recommended by the National Institute for Health and Clinical Excellence [28].

The difference in mean costs between active treatment and control groups together with the 95% confidence interval will be derived. The equivalence margin is pre-specified as £150. The equivalence will be declared between active and control groups in terms of secondary economic outcome if the 95% confidence interval falls within (-£150, +£150).

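### The 80% power claimed for cost equivalence is wrong: 186 per group gives about 40% under the plan's own 95% confidence interval rule

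*Protocol article*

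**What the plan says.** The Sample size section of the protocol article makes two calculations and takes the larger. The clinical one (Health Anxiety Inventory at one year) needs 152 patients after drop-out. The economic one sets the trial size: "With a sample size of 186 per group, the study will have 80% power to reject the null hypothesis". What is to be rejected is non-equivalence, with a margin of £150 in either direction, and the remaining inputs are stated as "assuming the expected difference in means is £0 and the common standard deviation is £580 (from pilot data"). No significance level is given for this calculation. The 186 per group become 466 randomised, "assuming a 20% drop-out by 24 months, leading to an estimated total of 372 completed with equal randomisation between groups". The section concludes that "the study is adequately powered to both detect the assumed difference in the primary outcome and assess the equivalence in the secondary economic outcome".

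The Statistical analysis section fixes the test. "The equivalence margin is pre-specified as £150", and equivalence is declared "if the 95% confidence interval falls within (-£150, +£150"). The Research objectives section adds that "the endpoint for this outcome is the cost of health service interventions at 2 years adjusted for baseline values".

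**The concern.** Requiring the whole 95% interval to lie inside ±£150 is the same as passing two one-sided tests, each at 2.5%. Power for such a rule must allow for failure at either limit and must use the 2.5% level. A quick check raises doubt. With 186 per group the standard error of the cost difference is about £60, so the 95% interval extends about £118 either side of the estimate. The estimate must then fall within roughly £32 of zero, about half a standard error. That cannot happen 80% of the time.

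Much depends on this figure. It triples the trial from 152 to 466 patients, and it supports the statement that the study is adequately powered for cost, the main secondary outcome. If the true power is far lower, a failure to show equivalence is the likely result even when costs are identical, and a reader who trusts the stated power could take that failure as a sign that costs differ.

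**Working it through.** **Inputs.** From the Sample size section: n = 186 completers per group, standard deviation £580, true difference £0, stated power 80%. From the Statistical analysis section: margin £150 on both sides, 95% interval.

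**Standard error.** SE = 580 × √(2/186) = £60.14. Margin/SE = 150/60.14 = 2.494.

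**Which test gives 80%?** For a single one-sided test, power = Φ(margin/SE − z).

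- One-sided 5%: Φ(2.494 − 1.645) = Φ(0.849) = 80.2%. With the t distribution it is 80.1% at 186 and 79.9% at 185, so 186 is the smallest size that reaches 80%.
- One-sided 2.5%: Φ(2.494 − 1.960) = Φ(0.534) = 70.3%; 80% needs 235 per group by the normal formula (236 with t).

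Of the variants tried, only the single one-sided 5% test reproduces both 186 and 80%.

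**Power for the equivalence rule.** With a true difference of zero and both limits required, power = 2Φ(margin/SE − z) − 1.

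| Rule | Normal formula | t-based | Simulation (400,000 draws) |
|---|---|---|---|
| 95% interval inside ±£150 (2.5% per side) | 2Φ(0.534) − 1 = 40.7% | 40.2% | 40.4% |
| 90% interval inside ±£150 (5% per side) | 2Φ(0.849) − 1 = 60.4% | 60.2% | 60.3% |

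**Size needed for 80% power.** n per group = 2 × [580 × (z + 1.282)/150]².

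- 95% interval: 314.2, so 315 (316 with t); 2 × 316/0.8 = 790 randomised.
- 90% interval: 256.1, so 257 (also 257 with t); 2 × 257/0.8 = 642.5, so 643 randomised.

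**Margin that 186 per group supports at 80% power.** With the 95% interval, (1.960 + 1.282) × 60.14 = about £195.

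**Numbers achieved.** The article reports 444 randomised and early drop-out below 10%. At 10% loss there are about 200 per group, and t-based power under the 95% rule is 46%. With no loss at all (222 per group) it is 55%.

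**Drop-out step.** 372/0.8 = 465, against 466 stated. This is correct apart from rounding.

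**Sensitivity to the standard deviation.** The £580 comes from a pilot in a single genitourinary clinic. As an illustration, £650 with 186 per group gives about 20% power under the 95% rule. Above about £736 the interval half-width itself exceeds £150, so equivalence could not be declared whatever the estimate.

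**The case against.** The arithmetic is hard to dispute, because every input is printed in the article. Four points can be made on the other side.

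1. **Baseline adjustment.** The Research objectives section says the cost endpoint is adjusted for baseline, which would reduce the residual standard deviation to 580 × √(1 − r²). No correlation r is given, so only a range can be shown. At 186 per group under the 95% rule, power is 48% at r = 0.3, 64% at r = 0.5, 75% at r = 0.6 and 80% at about r = 0.64 (residual standard deviation about £446). This stands as a qualification: the 40% is for an unadjusted comparison. It does not restore the stated figure, because the Sample size section uses £580 and claims no such gain, and the Statistical analysis section describes a plain difference in mean costs.
2. **One side may be what matters.** The Sample size section gives as its motivation that therapy should cost no more than control. But the hypothesis and the decision rule are both two-sided, and the upper limit of a 95% interval alone gives 70%, not 80%.
3. **The origin of 186 is inferred.** True: the article names neither the method nor the significance level. The match is exact, but the error does not depend on it, since neither equivalence version gives 80%.
4. **The consequences are limited.** The clinical outcome needs 152 patients and is unaffected. The cost-effectiveness and cost-utility analyses go ahead whatever the equivalence test shows, and nothing in the article says that non-equivalence will be read as a cost difference. This stands, and it limits the damage to the equivalence claim and to the justification of the sample size.

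**Conclusion.** The stated power is wrong as written. With 186 per group, a standard deviation of £580 and no true difference, the probability of declaring equivalence by the plan's 95% interval rule is about 40%, half the stated 80%. With a 90% interval it is about 60%, so the conclusion does not depend on the significance level that the Sample size section leaves out. The numbers actually randomised do not close the gap (46% at 10% loss, 55% with none).

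The 40% assumes approximately normal mean costs, equal variances and no baseline adjustment. Only a baseline correlation of about 0.64, which the article does not claim, would bring power to 80%. The statement of adequate power therefore holds for the clinical outcome but not for cost equivalence, which is the calculation that set the trial size.

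**What to change.** Correct the Sample size section to say that, with 186 per group, a standard deviation of £580, a true difference of £0 and no baseline adjustment, the probability that the 95% interval lies within ±£150 is about 40%, and that 80% applies only to a single one-sided 5% non-inferiority test. Confine the claim of adequate power to the clinical outcome. The remark that fewer than 466 patients would suffice if drop-out is lower should go too as far as cost is concerned, since it rests on the same target of 372 completers.

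Add to the Statistical analysis section that failure to show equivalence is not evidence that costs differ. If the analysis is still blind, it would also help to recompute the power with the pooled, arm-blind standard deviation, adjusted for baseline if that is the planned analysis. This cannot change the sample size, but it would tell readers what the equivalence test can show.

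The cost is a few sentences and one optional blinded calculation. No further patients are needed. The price is a less favourable power statement.

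### The £580 cost SD behind the 80% equivalence power has no stated period, and the written ±£150 rule gives about 41% unadjusted power even if it is a 24-month SD

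*Protocol article*

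**What the plan says.** All places are in the protocol article.

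- **Endpoint.** Under Sample size: "The sample size calculation for the economic evaluation was therefore based on the total costs over 24 months being equivalent". Research objectives defines the cost endpoint at 2 years and says it is adjusted for baseline values.
- **Power claim.** "With a sample size of 186 per group, the study will have 80% power to reject the null hypothesis" of non-equivalence, "assuming the expected difference in means is £0 and the common standard deviation is £580 (from pilot data". No significance level is given for this calculation.
- **Trial size.** The cost calculation sets it: "estimated as 466 patients, assuming a 20% drop-out by 24 months, leading to an estimated total of 372 completed with equal randomisation between groups". The HAI outcome alone would need 152. The section concludes that power is adequate for both outcomes.
- **Decision rule.** Under Statistical analysis: "The equivalence margin is pre-specified as £150", and equivalence is declared "if the 95% confidence interval falls within (-£150, +£150".
- **Pilot time references.** For HAI, "the standard deviation for the change of HAI at 1 year is 7.58 points". For cost, the Background says of the reductions seen in the only secondary-care trial that "these only became manifest in the six months after treatment had been completed [10". Neither gives the period of the £580.

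**The concern.** A cumulative cost SD has no meaning without its period, because costs summed over a longer time normally vary more. The endpoint runs over 24 months. The SD comes from a pilot for which the article shows only a 1-year HAI time point and a six-month post-treatment cost reference. If the £580 belongs to a shorter period and was not rescaled, the true analysis SD is larger than the one used for sizing.

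This input fixed the size of the whole trial, and the margin is narrow relative to it. A modest rise in SD makes the 95% interval wider than the full ±£150 band, so that equivalence could not be declared even with an observed difference of exactly £0. A failed rule would then reflect lack of precision, and readers relying on the printed 80% could take it for a finding about costs.

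**Working it through.** **Inputs.** n = 186 per group, true difference £0, SD £580 (Sample size); margin £150 and 95% CI rule (Statistical analysis). Normal approximation, with SE = SD × √(2/n).

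**1. Reproducing the printed 80%.** SE = 580 × √(2/186) = £60.1. A single one-sided 5% test has power Φ(150/60.1 − 1.645) = 80.2%, and 80% needs 185 per group. The printed figure therefore reproduces as a single one-sided 5% test. Dropout: 372/0.8 = 465, against 466 stated.

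**2. The written rule at SD £580.** Power = max(0, 2Φ(150/SE − 1.96) − 1). The half-width is 1.96 × 60.1 = £118 and power is 40.7%. An 80% power under this rule would need 315 per group.

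If £580 is an unadjusted 24-month SD, adjusting for a baseline cost with correlation r multiplies it by √(1 − r²):

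| r | SD | Power of written rule |
|---|---|---|
| 0 | £580 | 41% |
| 0.3 | £553 | 49% |
| 0.5 | £502 | 64% |
| 0.7 | £414 | 87% |

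**3. Where the rule becomes unreachable.** The half-width equals £150 at SD = 150/(1.96 × √(2/n)):

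- 186 per group: £738, which is 27% above £580
- 200 per group (444 randomised, 10% loss): £765
- 233 per group (466, no loss): £826

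**4. If £580 is a 12-month SD (assumption; equal yearly variances).** Unadjusted SD₂₄ = 580 × √(2(1 + ρ)), where ρ is the year-to-year correlation:

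| ρ | SD₂₄ | Half-width at 186 per group | Power of written rule |
|---|---|---|---|
| 0 | £820 | £167 | about 0% |
| 0.5 | £1,005 | £204 | about 0% |
| 1 | £1,160 | £236 | about 0% |

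Discounting year 2 at 3.5% changes the SD range to £806–£1,140 and the half-width to £164–£232. At £820, 200 per group gives £161 and 233 per group gives £149, just inside the margin. An unadjusted SD below £738 would need ρ below about −0.19, since 738²/(2 × 580²) − 1 = −0.19.

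**5. The same case with baseline adjustment.** Assume baseline is a comparable one-year cost and all three pairwise correlations equal ρ. The residual SD is then 580 × √(2 + 2ρ − 4ρ²):

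| ρ | Adjusted SD | Power of written rule, 186 per group |
|---|---|---|
| 0 | £820 | 0% |
| 0.3 | £868 | 0% |
| 0.5 | £820 | 0% |
| 0.6 | £769 | 0% |
| 0.7 | £696 | 9% |
| 0.8 | £592 | 37% |
| 0.9 | £434 | 83% |

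The SD crosses £738 at ρ of about 0.65.

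**The case against.** The strongest objection is that nothing in the article shows £580 to be a 12-month SD. The figure follows directly on a statement about 24-month totals and may already have been put on that basis. Its derivation lies in a cited source, and a condensed article may leave such detail to the full protocol. This stands against the stronger reading that a reader might infer, namely that a shorter-period SD was used and the rule therefore cannot be met. The 1-year time point belongs to HAI, the only pilot cost reference is to six months, and neither is attached to the £580.

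The planned baseline adjustment is a second good objection. High year-to-year correlation gives the largest unadjusted SDs but also makes adjustment most effective, so zero power across the whole range is not established. What remains is that, on the 12-month assumption, adjustment rescues the rule only at high correlations.

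Third, the low power at £580 comes from sizing on a one-sided 5% test rather than from the SD. That is true, and it means the written rule has no slack to absorb a larger SD.

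Finally, the article does not treat a failed rule as evidence against equivalence, and it already plans to report the difference with its interval and a net-benefit analysis. That limits the harm but does not repair the power statement. The move from one genitourinary clinic to five other specialties might also change the SD, but the article gives no figure for this and no weight is placed on it here.

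**Conclusion.** The point holds in conditional form. Without any assumption about the period, the article gives an SD of unstated period for a 24-month endpoint, and the written rule at 186 per group has about 41% unadjusted power at £580, not 80%. Above an analysis SD of about £738 it has none.

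The larger loss depends on an assumption. If £580 is an unscaled 12-month SD with equal yearly variances, unadjusted power is about 0%, and adjusted power is zero unless the common correlation exceeds about 0.65. If £580 is already a 24-month SD, there is no loss from this cause, and a baseline correlation of 0.7 would bring power above 80%. The documents do not settle which case applies, so it would be wrong to conclude that the trial cannot show equivalence. The claim of adequate power for the economic outcome is nevertheless unsupported as written.

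**What to change.** In Sample size:

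- State the period the £580 covers.
- Put the SD on the 24-month basis. Either rescale it over a stated range of year-to-year correlations, or use the blinded pooled SD of the trial's own cost data. In both cases take it net of the baseline adjustment.
- Restate the power of the 95% CI rule at the expected number of completers, and withdraw the statement of adequate power for the economic outcome if the result is below 80%.

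In Statistical analysis, add that an interval extending beyond a margin but not lying wholly outside ±£150 is inconclusive. The cost conclusion is then drawn from the estimated difference, its interval and the net-benefit analysis already planned. The wording should not dismiss every interval with a half-width above £150: an interval of £160 to £500, for example, has a half-width of £170 but lies wholly outside the margin and is clear evidence of non-equivalence.

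The cost is a few sentences and one blinded SD calculation, with no extra patients. The downside is a less favourable stated power.
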